### Statistical analysis

#### Sample size

From a study that enrolled a similar population, the mean and standard deviation of antibiotic-free days was: mean (SD), 14 (9) [43]. A 25 % increase in antibiotic-free days would be clinically significant and feasible if LF has the expected biological activity. To detect a 25 % increase in antibiotic-free days to 17.5 days in the intervention arm with 80 % power at a two-sided alpha of 0.05, a sample size of 210 (105 subjects per arm) is required. We believe that this sample size will be adequate to reliably assess all feasibility and laboratory outcomes but may not be powered for all clinical outcomes.

#### Analysis of primary and secondary outcomes

The main analysis will provide a histogram showing the distribution of the antibiotic-free days per arm. Although the antibiotic-free days will not be normally distributed, the sample is large enough that the mean will be approximately normally distributed, so the mean difference with corresponding 95 % confidence intervals and *p* values will be estimated by an analysis of variance blocking by site. A sensitivity analysis will use an exact permutation test stratified by site to confirm the main conclusion. For transparency we will report both the primary and sensitivity analysis.

Feasibility outcomes will not be compared by arm but will be provided overall using descriptive statistics (recruitment rates, adherence and completeness proportions and mean time needed to capture required data). Since there are multiple clinical outcomes that may have low power, we will avoid formal hypothesis testing and focus on presenting the between-arm difference in means or proportions with 95 % confidence intervals. All clinical analyses will control for site.

The distribution of the laboratory and biochemical outcomes will be depicted by arm over time using clustered boxplots. Statistical significance between arms at each time point will be tested by the Wilcoxon-rank sum test, but the multiplicity of tests and clinical important of differences will be considered when interpreting statistical significance. All analysis will adhere to the intent-to-treat principle. We expect the amount of missing data to be trivial (less than 5 %), but details of any missing data will be reported.

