### Secondary outcomes

*Feasibility (recruitment rates*, *protocol adherence*, *data completeness*, *and time required to capture data)*: the goal for the recruitment rate will be an average of 0.75 patients per week/per site. Protocol adherence will be considered successful if more than 80 % protocol adherence is achieved. Evaluation of protocol adherence will include administration of study medications, obtaining biological samples and carrying out laboratory testing protocols. The goal for data completeness is 100 %, but success will be defined at knowing the status of more than 95 % of the 28-day outcomes. Lastly, the time needed to capture required data will be used to determine the budget and feasibility of a future definitive RCT*Clinical outcomes*: antibiotic utilization will be measured by the prescription of new antibiotics after 72 h of admission to ICU, and number of defined daily doses (DDD) of antibiotics. Blinded central adjudication of nosocomial infection (longer than 72 h from admission to ICU) will be determined using standardized definitions and procedures. Change in organ function post randomization will be measured using the Sequential Organ Failure Assessment (SOFA) score [39]. We will also record hospital and ICU length of stay, and hospital survival and 90-day mortality*Laboratory and biochemical outcomes*: the effects of LF will be evaluated using biomarker analysis, i.e., measurement of levels of sequential PCT, CRP, and IL-6 at baseline, day 3, day 7 and then weekly until 28 days post randomization. Gastrointestinal permeability will be measured using the Lactulose/Mannitol Ratio at day 5 [40, 41]. Immune function will be evaluated based on the production of tumor necrosis factor alpha (TNF-α) in response to an LPS stimulation assay [42]. Rates of tracheal colonization will be determined by the number of tracheal samples positive for potential pathogens*Genomics substudy*: the biological mechanisms of LF action will be explored using gene expression profiling. In a subset of patients (continuously recruited from one study site), an additional tube of blood will be collected at the abovementioned time points for RNA extraction and gene expression profiling. Bioinformatic analyses will examine differences in gene expression at baseline between control and treatment groups, changes in the treatment group in response to therapy, and differences between patients with and without the primary outcome

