#### Subgroup and interim analysis

Due to conflicting results on the effects of LF when used as a treatment for sepsis [44, 45] a priori, we will conduct a subgroup analysis of patients presenting with sepsis [46]. No formal interim analyses are planned.

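### The primary ANOVA adjusts for site only; adding sepsis at presentation and baseline SOFA would gain precision at almost no cost

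*Protocol article*

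**What the plan says.** All references are to the protocol article.

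- *Analysis of primary and secondary outcomes*: the mean difference in antibiotic-free days is "estimated by an analysis of variance blocking by site". The sensitivity analysis is an exact permutation test, also stratified by site. The clinical analyses likewise control for site, and no other adjustment is named.
- *Random allocation*: site is the only stratification factor.
- *Subgroup and interim analysis*: "we will conduct a subgroup analysis of patients presenting with sepsis". This was decided in advance, so sepsis status at entry has to be recorded.
- *Secondary outcomes*: "Change in organ function post randomization will be measured using the Sequential Organ Failure Assessment (SOFA) score". A change score implies a baseline score.
- *Sample size*: the plan aims at a rise from 14 to 17.5 days and is sized for 80% power with a two-sided 5% test. It concludes that "a sample size of 210 (105 subjects per arm) is required". The calculation takes no credit for covariates.
- *Exclusion criteria*: neither sepsis nor current antibiotic treatment excludes a patient.

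**The concern.** The outcome counts days alive and off antibiotics up to day 28, and the agent is being tested for prevention. Patients who enter with sepsis are likely to spend antibiotic days on an infection that is already present. Patients with more organ failure are more likely to die. Both features are therefore plausible predictors of the count, whichever arm the patient is in.

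If so, a model with site alone leaves explainable variation in the error term. The interval for the treatment effect is then wider than it needs to be. Randomization does not balance these factors beyond site, so the estimate in this one trial can also move with a chance difference between arms. Precision matters here because the result will inform whether a larger trial goes ahead, and the sample size has almost no margin above 80% power.

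**Working it through.** **Inputs from *Sample size*.** Control mean 14 days, SD 9, target 17.5 days (difference 3.5), two-sided alpha 0.05, power 80%, 105 per arm.

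**Step 1: reproduce the plan's figure.**
- Normal approximation: n per arm = 2 × (1.960 + 0.842)² × 9² / 3.5² = 103.8, so 104 per arm and 208 in total.
- Noncentral t: power is 79.7% at 104 per arm and 80.1% at 105 per arm, which gives the stated 210.

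The planned sample size is correct for an analysis without patient-level covariates.

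**Step 2: effect of adjustment.** Let R² be the share of outcome variance that the added covariates explain. The documents do not give it, so it is an assumption, shown as a range.
- Residual SD = 9 × √(1 − R²)
- Standard error = residual SD × √(2/105)
- Half-width of the 95% interval = 1.96 × standard error
- Equivalent unadjusted sample size = 210 / (1 − R²)

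| Assumed R² | Residual SD | Power for 3.5 days (noncentral t) | Half-width (days) | Equivalent total N |
|---|---|---|---|---|
| 0 | 9.00 | 80.1% | 2.43 | 210 |
| 0.05 | 8.77 | 82.1% | 2.37 | 221 |
| 0.10 | 8.54 | 84.0% | 2.31 | 233 |
| 0.20 | 8.05 | 88.0% | 2.18 | 262 |

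Using t in place of 1.96 gives half-widths of 2.45 to 2.19 days across the same range. Removing seven residual degrees of freedom (four for five sites, three for covariates) changes power by well under 0.1 percentage points.

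**Step 3: is the range reasonable?** Take a binary factor with an assumed prevalence of 50%. If it shifts the outcome by g days, it explains g² × 0.25 / 81 of the variance. That is 2.8% for 3 days, 7.7% for 5 days and 15.1% for 7 days. These shifts are assumptions too.

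**Step 4: chance imbalance.** For the same factor, the between-arm difference in prevalence has SD √(2 × 0.25 / 105) = 6.9 percentage points. A 1.96-SD imbalance is 13.5 points. It would move the unadjusted estimate by 0.135 × g: 0.41, 0.68 or 0.95 days for shifts of 3, 5 or 7 days, against a target of 3.5 days.

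**Step 5: missing outcomes.** The analysis section expects less than 5% missing data, and the sample size carries no allowance for it. With 100 analysed per arm (about 5% lost), power is 78.1% without covariates and 80.2% with R² = 0.05. A weak set of predictors would therefore offset that loss.

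**The case against.** The strongest reply is that nothing in the plan is wrong. Site is the only stratification factor and the model blocks on it, so analysis and randomization agree. The estimate is unbiased over randomization and the type I error is kept. The planned power is delivered, and the gain rests on an R² that the documents do not supply. All of this stands, and it limits how far the point can go.

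Three stronger readings are tempting, and the documents do not support them.

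- *The trial is underpowered because it does not adjust.* Step 1 shows that the site-only analysis reaches 80.1%. What is lost is an available gain.
- *Unadjusted chance imbalance biases the result.* The standard error of the randomized comparison already allows for such imbalance. Leaving it unadjusted costs precision, not validity.
- *Antibiotic status at randomization is already recorded, so it can be used at no cost.* The article mentions antibiotics only as outcomes: antibiotic-free days after randomization, new prescriptions after 72 hours in ICU, and defined daily doses. Daily follow-up to day 28 does not establish that a baseline status is captured.

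Two further objections carry less weight. The statistical analysis plan, which is not shown, may contain an adjusted supportive analysis. The article nevertheless states the primary model explicitly, and the recommendation concerns that model. The sepsis subgroup does show the result in those patients, but it does not sharpen the overall estimate.

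**Conclusion.** The point holds as an efficiency improvement, not as an error. The primary analysis is valid as written and does what the sample size asks of it. It leaves out one baseline factor that must be known (sepsis at presentation) and one that is implied (baseline SOFA), both of which plausibly predict the outcome.

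Under an assumed R² of 0.05 to 0.20, adjustment would add about 2 to 8 percentage points of power for 3.5 days. It would narrow the 95% interval half-width by 0.06 to 0.25 days (2.43 − 2.37 and 2.43 − 2.18). At the low end the gain is small. The two covariates may also overlap, since patients with sepsis often have organ dysfunction, so their joint R² should not be taken as the sum of two separate ones.

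**What to change.** Before unblinding, pre-specify the primary model as an ANCOVA of antibiotic-free days on arm, site, sepsis at presentation (yes/no) and baseline SOFA. Add antibiotic status at randomization only if it is confirmed to be a baseline item on the case report form. Define every covariate from information that predates randomization. Keep the site-only ANOVA and the site-stratified permutation test as sensitivity analyses, and report all of them.

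The cost is one sentence in the analysis plan and two residual degrees of freedom (three with antibiotic status). A stated rule is also needed for missing baseline values, so that no randomized patient drops out of the primary analysis. No new data are needed for sepsis, nor for SOFA if the implied baseline score is recorded.

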### Random allocation

A password-protected web-based central randomization system is used to allocate patients to study treatments such that investigators, research staff and patients are blinded to the next allocation and an audit trial is maintained. Clinicians will remain blinded during the study, which will be maintained by administering LF or placebo in opaque syringes such that the placebo and active solutions are indistinguishable from each other. Randomization will be stratified by site using permuted blocks of variable size. The randomization list will be computer-generated by the trial biostatistician using SAS (SAS Inc., Cary, NC, USA) and securely stored by the study biostatistician and the IT manager of the central randomization system.

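### Change in SOFA is to be compared as a difference in means with site the only adjustment named; adding baseline SOFA to the model would usually narrow the interval at no data cost (minor)

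*Protocol article*

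**What the plan says.** The Secondary outcomes section of the Protocol article lists organ function among the clinical outcomes: "Change in organ function post randomization will be measured using the Sequential Organ Failure Assessment (SOFA) score".

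The section Analysis of primary and secondary outcomes gives one method for all clinical outcomes. Because several of them may have low power, it plans no formal tests for them and will instead "focus on presenting the between-arm difference in means or proportions with 95 % confidence intervals. All clinical analyses will control for site". No baseline covariate is named for any outcome. The primary analysis is likewise an analysis of variance with site as its only blocking factor.

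Under Random allocation: "Randomization will be stratified by site using permuted blocks of variable size". No other stratification factor is given, so baseline SOFA is not balanced by design.

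**The concern.** A change in SOFA cannot be computed without a baseline SOFA, so that value will be on file for every patient who contributes to the outcome. Applied literally, the stated method gives a between-arm difference in mean change, controlled for site. That is not the same as adjusting for baseline. A change score subtracts the whole baseline value, whereas regression adjustment subtracts only the part that predicts follow-up. When the two differ, the change score has extra variance, and part of any chance difference in baseline severity passes into the estimate.

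At stake is the width of one confidence interval. The article accepts that the clinical outcomes may be underpowered and relies on intervals instead of tests, and the results are meant to inform a larger trial. When the interval is the result, avoidable width is worth removing.

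**Working it through.** **The plan's own figure.** Sample size section: control mean 14, SD 9, target 17.5 (difference 3.5), "with 80 % power at a two-sided alpha of 0.05". Normal approximation: n per arm = 2 × (1.960 + 0.842)² × 9² / 3.5² = 103.8, so 104. The t-test version gives 104.8, so 105 per arm and 210 in total, as stated. Power at 105 per arm is 80.4 % (normal) or 80.1 % (t). This figure concerns antibiotic-free days. It is used below only for the 105 per arm and otherwise has no bearing on SOFA.

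**Inputs for SOFA.** The article gives no SOFA SD, no correlation and no assessment day. Assumptions: a single follow-up value; correlation ρ within arm and site, varied from 0.3 to 0.9; baseline SD s; and, to begin with, the same SD at follow-up.

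**Precision with equal variances.**

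- Change score: variance per patient 2(1 − ρ)s².
- Baseline-adjusted (ANCOVA): variance per patient (1 − ρ²)s².
- Ratio, ANCOVA to change score: (1 + ρ)/2. The interval-width ratio is its square root.
- With 105 per arm, half-width = 1.96 × √(2/105) × √(variance per patient), where √(2/105) = 0.138.

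**Chance imbalance with equal variances.** A baseline difference d between arms shifts the expected change-score difference by (ρ − 1)d, so the arm that starts sicker appears to improve more. A one-standard-error imbalance is d = 0.138 s.

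| ρ (assumed) | Variance ratio | Width ratio | Interval narrower by | Half-width, change score (in s) | Half-width, ANCOVA (in s) | Shift from 1-SE imbalance (in s) |
|---|---|---|---|---|---|---|
| 0.3 | 0.65 | 0.806 | 19 % | 0.320 | 0.258 | −0.097 |
| 0.5 | 0.75 | 0.866 | 13 % | 0.271 | 0.234 | −0.069 |
| 0.7 | 0.85 | 0.922 | 8 % | 0.210 | 0.193 | −0.041 |
| 0.9 | 0.95 | 0.975 | 3 % | 0.121 | 0.118 | −0.014 |

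For scale only: if s were 4 SOFA points (an assumption), a one-standard-error imbalance would be 4 × 0.138 = 0.55 points. The shift would be 0.39, 0.28 and 0.17 points at ρ of 0.3, 0.5 and 0.7.

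**Unequal variances.** Let the follow-up SD be k times the baseline SD. In units of baseline variance:

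- Change score: 1 + k² − 2ρk.
- ANCOVA: k²(1 − ρ²).
- Difference: (1 − ρk)², which is never negative and is zero when ρk = 1.

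At ρ = 0.6 and k = 1.5 (illustrative): change score 1 + 2.25 − 1.80 = 1.45; ANCOVA 2.25 × 0.64 = 1.44; ratio 0.99. The gain has nearly vanished. The carry-over is now (ρk − 1)d = −0.1d, also small. Apart from the one degree of freedom spent, adjustment does not lose precision, but its benefit depends on both ρ and k.

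**The case against.** The strongest objection is that the article does not fix an unadjusted SOFA model. The sentence on site covers every clinical outcome, including antibiotic use, infection, length of stay and mortality. It does not say that site is the only covariate, and it does not exclude baseline SOFA. Covariates for one secondary outcome are often left to the SAP, which is not shown. This stands in part. A reader might infer that baseline SOFA has been deliberately left out, and the text does not support that. It does, however, name an estimator and one adjustment for all clinical outcomes, so proposing a better version of that stated method is fair. If a SAP already includes baseline SOFA, only confirmation is needed.

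Second, the article does not define the change as one follow-up value minus baseline. That stands as a limit on the arithmetic, which describes the two-point case. Any measure of change still needs a baseline value.

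Third, the size of the gain depends on assumed correlations and variances. This stands in full, as the unequal-variance example shows.

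Three stronger readings are tempting and should be resisted:

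- A reader might infer that the planned estimate is biased. It is not: under randomization the imbalance is chance error, and the unadjusted interval already allows for it.
- A reader might infer that the whole of a baseline imbalance enters the result. With equal variances only the share (1 − ρ) does, with its sign reversed.
- A reader might turn the variance ratio into lost power. The article plans no formal test for this outcome, so interval width is the relevant measure.

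**Conclusion.** The point holds as a minor, optional improvement. As written, the analysis of change in SOFA is valid and unbiased under randomization, but generally less precise than a baseline-adjusted one. Assuming equal baseline and follow-up variances, adjustment would narrow the 95 % confidence interval by about 19 % at ρ = 0.3, falling to about 3 % at ρ = 0.9, and would remove the (1 − ρ) share of chance baseline imbalance. If follow-up variance is much larger than baseline variance, the gain can be close to zero. None of these correlations or variances comes from the article. The primary conclusion, error rates, sample size and feasibility criteria are unaffected.

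**What to change.** Add one sentence to Analysis of primary and secondary outcomes, or confirm that the SAP already contains it: the SOFA outcome will be analysed with a linear model containing treatment arm, baseline SOFA and site, and the adjusted mean difference will be reported with its 95 % confidence interval. Once baseline is in the model, using follow-up SOFA or its change as the dependent variable gives the same treatment estimate, so the outcome can still be described as a change. The result is still a difference in means controlled for site. The cost is that sentence and one degree of freedom; no new data, visits or patients are needed.

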### Follow-up

Patients will be followed daily until day 28. Mortality will be determined for the ICU stay, hospital stay, and at 90 days. All patients will have blood samples drawn for biomarkers (C-reactive protein (CRP), procalcitonin (PCT), and IL-6), as well as for genome-wide expression profiling, at baseline and on days 3, 7, 14, 21, and 28. Cytokines will be measured using multiplex enzyme-linked immunosorbent assays (ELISAs), with samples prepared on site and shipped to a central laboratory for processing. Blood for gene expression analysis will be collected in PAXgene tubes, frozen according to the manufacturer’s protocol, and shipped to a central genomics facility for ribonucleic acid (RNA) extraction and expression profiling using the Affymetrix PrimeView microarray [33, 34]. Tracheal samples for bacterial cultures will be obtained at baseline and on days 3, 7, 14, 21, and 28. In addition, given the nature of the intervention, no specific provisions have been made for ancillary or post-trial care of participants.

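### The laboratory outcomes are compared by an unadjusted Wilcoxon test at each time point, which leaves out the measured baseline and the site strata and so gives up precision; multiplicity is handled only informally

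*Protocol article*

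**What the plan says.** Under Analysis of primary and secondary outcomes, the laboratory and biochemical outcomes are to be plotted by arm over time, and then: "Statistical significance between arms at each time point will be tested by the Wilcoxon-rank sum test". The same sentence goes on to say that "the multiplicity of tests and clinical important of differences will be considered when interpreting statistical significance".

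The Secondary outcomes section plans "measurement of levels of sequential PCT, CRP, and IL-6 at baseline, day 3, day 7 and then weekly until 28 days post randomization". The Follow-up section gives the same days ("at baseline and on days 3, 7, 14, 21, and 28") and states that "All patients will have blood samples drawn for biomarkers".

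On site, Random allocation says "Randomization will be stratified by site using permuted blocks of variable size". The primary ANOVA blocks by site, its permutation check is stratified by site, and for the clinical outcomes "All clinical analyses will control for site". The laboratory test is described in the next paragraph, with no mention of site or baseline.

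On missing data: "We expect the amount of missing data to be trivial (less than 5 %), but details of any missing data will be reported".

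**The concern.** The article names a method here, so this is a fixed choice and not a detail left to a fuller document. It raises two separate issues.

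- **Precision.** Baseline marker levels often predict later levels in the same patient, and sites may differ in case mix. A test that uses neither leaves explainable variation in the noise.
- **Repeated testing.** For the clinical outcomes the authors avoid formal tests, because there are several and power may be low. For the laboratory outcomes they test at every time point.

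The Background section presents the biomarker and mechanistic data as support for the primary outcome in a trial meant to inform whether a larger study goes ahead. A real signal missed through imprecision, or an isolated small p value read as a signal, could colour that judgement.

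**Working it through.** **The plan's own figure.** Inputs from Sample size: SD 9, difference 17.5 − 14 = 3.5, 80 % power, two-sided alpha 0.05. The normal formula gives n = 2 × (1.960 + 0.842)² × 9² / 3.5² = 103.8, so 104 per arm. The noncentral t version gives 105 per arm (power 0.801), or 210 in total, as stated. That section calls 210 adequate for the laboratory outcomes too, but gives no laboratory SD or effect size.

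**Precision.** Adjusting for a baseline value with correlation ρ multiplies the variance by 1 − ρ². The article gives no ρ, so a range is assumed. The reference is a standardized effect of 0.387, which 105 per arm detects with 80 % power by a z-test.

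| Assumed ρ | Variance factor | Unadjusted sample worth (1/factor) | Power after adjustment | Per arm for 80 % |
|---|---|---|---|---|
| 0.3 | 0.91 | 1.10 | 84 % | 96 |
| 0.5 | 0.75 | 1.33 | 90 % | 79 |
| 0.6 | 0.64 | 1.56 | 94 % | 68 |

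A simulation used 210 patients, five equal sites, allocation balanced within site and 3,000 runs per setting. Between-site SD is in units of the within-site SD.

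- Planned Wilcoxon test: power 76 to 78 % with between-site SD of 0 to 0.3, and 71 to 72 % at 0.5.
- Rank ANCOVA with baseline and site: 81 to 82 % at ρ = 0.3, and 88 to 89 % at ρ = 0.5.

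**Error rate of a single test.** With no treatment effect, the Wilcoxon test rejected in 4.8 to 5.6 % of runs without site differences and in 3.2 to 4.5 % with them. Simulation error is about √(0.05 × 0.95 / 3000) = 0.4 points. Leaving out baseline and site therefore does not inflate the error rate; with site differences the test is somewhat conservative.

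**Multiplicity.** Three markers × five post-baseline days = 15 tests.

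- Independent: 1 − 0.95¹⁵ = 53.7 %.
- Assumed correlations of 0.3 to 0.7 over time and 0.3 to 0.5 between markers (multivariate normal simulation): 34 to 49 %.
- If baseline is also tested (18 tests): 1 − 0.95¹⁸ = 60.3 %, or 37 to 55 % under the same correlations.

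**Availability at late days.** The article gives no death or discharge rate for this trial. If 80 % of 105 per arm (84) can be sampled, the 80 % power falls to 71 %; at 60 % (63) it is 58 %. A second simulation had no biomarker effect, ρ = 0.5, and availability that depended on severity:

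| Difference between arms in share sampled | Wilcoxon rejects | Adjusted rank ANCOVA rejects |
|---|---|---|
| 0 points | 5.1 to 5.2 % | 5.3 to 5.5 % |
| 10 points | 6.9 to 8.0 % | 6.6 to 7.1 % |
| 20 points | 14.6 to 17.0 % | 12.5 to 14.5 % |

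Adjustment for baseline and site does little for this problem.

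**The case against.** The strongest defence is that a Wilcoxon test between randomized arms is valid and robust to skewed markers, so the choice costs only efficiency. That stands. A reader might infer that ignoring baseline and site invites false positives; the null rejection rates above show that it does not.

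A reader might also infer that multiplicity is overlooked. It is not: the sentence naming the test says that it will be weighed. What remains is that no rule is attached, so the error rate is not controlled. The 54 % figure assumes independence, which is unlikely for repeated inflammatory markers in the same patients; under the assumed correlations the chance stays below one half. Whether each time point includes baseline is not stated, so the count of 18 is only a possible reading.

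The correlations are assumed, and one value is unlikely to hold from day 3 to day 28. This limits the size of the gain, mainly at late days, but not its direction.

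A further tempting inference is that the late comparisons are biased or breach intention to treat. The documents do not establish this. They do not say that sampling stops at discharge, they give no attrition figures, and comparing available patients by assigned arm does not in itself contradict the principle. The two adult sepsis trials in the Discussion had 28-day mortality of 14.4 to 26.9 % and 18 to 25 %. This makes it doubtful that fewer than 5 % will lack a day 28 sample, but that was a different population.

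Finally, these are secondary outcomes, and no decision rule in the article rests on a biomarker p value.

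**Conclusion.** The point holds as one of efficiency and of unstructured multiplicity, not as a flaw in validity. The stated laboratory test uses neither a baseline that is collected nor a stratification factor that the other between-arm analyses respect. The cost is 9 to 36 % of the variance for assumed baseline correlations of 0.3 to 0.6, plus a further loss if sites differ. The chance of at least one false positive across the 15 post-baseline biomarker tests is 54 % under independence and about 34 to 49 % under the assumed correlations, with only informal handling.

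Death before a sampling day is a separate limit on the late comparisons. It would distort them only if severity-related availability differed between arms, which the documents neither show nor exclude. The change is worth making because it needs no new data, but the trial's primary conclusion does not depend on it.

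**What to change.** - For CRP, PCT and IL-6, estimate the arm difference with adjustment for the baseline value and site: either a mixed model on log values with arm, day and arm-by-day terms, or rank ANCOVA at each day. Let the baseline coefficient vary by day, since the correlation may weaken.
- Keep a site-stratified (van Elteren) rank test as a check, and use it for outcomes measured once, such as the day 5 permeability ratio.
- State that baseline values are described and not tested.
- Before unblinding, name one main post-baseline day per marker. The article offers no basis for choosing it, so the reason should be recorded. Present the other days as estimates with 95 % confidence intervals and no significance claims, as for the clinical outcomes. Three main tests still carry 1 − 0.95³ = 14.3 % if independent, so label them exploratory or apply a Holm correction.
- Report the numbers alive and sampled by arm at each day, and describe late-day results as comparisons among patients alive and sampled. Neither covariate adjustment nor a missing-at-random model removes truncation by death.

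The cost is a paragraph of analysis-plan text and modest programming. The mixed model adds a log-scale assumption, which the rank-based check covers.
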